### ***Participant acceptability of the study and proxy response measurement***

Participant's acceptability of the study is a primary endpoint under desirability. This will be assessed at the time of participant's last visit (Week 12 or Week 24 if the patient opts in to the study extension phase). A set of 3 questions will be asked to evaluate if participants find the study acceptable. In addition, information on whether

participant's required assistance to complete study tools will be evaluated by one screening question and two follow up questions if they answer 'No' to the screening question.

## **6.8 Caregiver reported measure**

### ***Carer Experience Scale***

The Carer Experience Scale (CES) is a profile measure of the caring experience for use in economic evaluation.

 It focuses on 'care-related quality of life' rather than health-related quality of life, comprising attributes that are pertinent to unpaid carers. The tool comprises six attributes: activities, support from family and friends, assistance from organisations, fulfillment, control, and getting-on with the care recipient. This will be administered to caregivers at the start and cessation of treatment, i.e. at baseline (Visit 2) and Week 12 or 24 (Visits 5 or 7, if patient opts into extension phase).

### ***EuroQol 5-Level 5-Dimensions – Quality of Life Caregiver***

Quality of life of caregivers will be measured using the EQ-5D-5L. EQ-5D-5L assesses mobility, self-care, usual activities, pain / discomfort, anxiety / depression according to three levels of severity (1 = no problems; 2 = some or moderate problems; 3 = extreme problems), plus a VAS of current health-related quality of life, scored 0 – 100. This will be administered to caregivers at the start and cessation of treatment of the person they provide care for, i.e. at baseline (Visit 2) and Week 12 or 24 (Visits 5 or 7, if patient opts into extension phase).

### ***Caregiver diary***

Caregivers will be asked to record basic demographic and caregiver details once only at baseline and a repeated series of questions on completion of the study. This will enable changes in the caregiving needs to be assessed.

### ***Unplanned healthcare costs.***

Caregivers will also be asked to include resource use to estimate cost of indirect and informal care in their diary. This will help assess the proposed measures for a health economic analysis (cost consequence) in any subsequent phase III study. Questions including time off work, time spend in-home nursing or accompanying to hospital, out-of-pocket expenses, etc.

## **6.9 Participant retention and follow-up**

Evidence of the study's responsiveness to participant needs and flexibility is critical for participant retention.

Study staff are trained to expect that at times, it will be necessary to reschedule evaluations and appointments. Ensuring that the study involves minimal burden to participants is crucial in this. The study assessments are tabulated below.

**Table 6-1 Schedule of Study Assessments for patients (Screening to Week 12 and optional extension – Weeks 13-24)**

| Assessment                                               | Screening | Baseline | Visit Day
Treatment
Period |   |    | Extension |    | Exit/ Early
Termination
(Withdrawal) a | Follow-
up b |
|----------------------------------------------------------|-----------|----------|----------------------------------|---|----|-----------|----|---------------------------------------------------------|----------------------------|
| Week                                                     |           |          | 4                                | 8 | 12 | 18        | 24 |                                                         |                            |
| Visit                                                    | 1         | 2        | 3                                | 4 | 5  | 6         | 7  |                                                         |                            |
| Informed consent                             | X         |          |                                  |   |    |           |    |                                                         |                            |
| Randomisation                                            |           | X        |                                  |   |    |           |    |                                                         |                            |
| Medical history/ demographic/ clinical information       | X         |          |                                  |   |    |           |    |                                                         |                            |
| Physical examination (complete/dedicated)                | X         |          | X                                | X | X  | X         | X  | X                                                       |                            |
| AKPS                                                     | X         | X        | X                                | X | X  | X         | X  | X                                                       |                            |
| Vital signs                                              | X         |          | X                                | X | X  | X         | X  | X                                                       |                            |
| SBT (Short Blessed Test)                                 | X         |          |                                  |   |    |           |    |                                                         |                            |
| 12-Lead ECG                                              | X         |          | X                                | X | X  |           |    | X                                                       |                            |
| Chemistry/Hematology                                     | X         |          | X                                |   | X  |           | X  | X                                                       |                            |
| CRP                                                      |           | X        | X                                |   | X  |           | X  | X                                                       |                            |
| IL-6                                                     |           | X        | X                                |   | X* |           | X  | X                                                       |                            |
| Urine pregnancy                                          | X         | X        |                                  |   | X  |           |    |                                                         |                            |
| FAACT A/CS questionnaire                                 | X         | X        | X                                | X | X  | X         | X  | X                                                       |                            |
| Prior and concomitant medication data                    | X         | X        | X                                | X | X  | X         | X  | X                                                       | X                          |
| Harms                                                    |           | X        | X                                | X | X  | X         | X  | X                                                       | X                          |
| Survival (overall and cancer-specific) –date of death    |           | X        | X                                | X | X  | X         | X  | X                                                       | X                          |
| Height                                                   |           | X        |                                  |   |    |           |    |                                                         |                            |
| Body weight (from which BMI will be calculated)          |           | X        | X                                | X | X  | X         | X  | X                                                       |                            |
| Self-reported weight loss in the last 1, 6, 12 months    |           | X        |                                  |   |    |           |    |                                                         |                            |
| BIA (Bio-electrical impedance)                           |           | X        |                                  |   | X* |           | X  | X                                                       |                            |
| DEXA scan                                                |           | X        |                                  |   | X* |           | X  | X                                                       |                            |
| CT scan                                                  |           |          | X^                               |   |    |           |    | X^                                                      |                            |
| FACIT-F questionnaire                                    |           | X        |                                  | X | X  |           | X  | X                                                       |                            |
| GIC (Global Impression of Change)                        |           |          | X                                | X | X  |           | X  | X                                                       |                            |
| CGI-S (Clinical Global Impression of disease severity)   |           | X        | X                                | X | X  | X         | X  | X                                                       |                            |
| CGI-I (Clinical Global Impression of improvement/change) |           |          | X                                | X | X  | X         | X  | X                                                       |                            |

| Assessment                                                     | Screening | Baseline | Visit Day
Treatment
Period |   |          | Extension |          | Exit/ Early
Termination
(Withdrawal) a | Follow-
up b |
|----------------------------------------------------------------|-----------|----------|----------------------------------|---|----------|-----------|----------|---------------------------------------------------------|----------------------------|
| Week                                                           |           |          | 4                                | 8 | 12       | 18        | 24       |                                                         |                            |
| Visit                                                          | 1         | 2        | 3                                | 4 | 5        | 6         | 7        |                                                         |                            |
| EQ-5D-5L - quality of life                                     |           | X        |                                  | X | X        |           | X        | X                                                       |                            |
| ICECAP-A - quality of life                         |           | X        |                                  | X | X        |           | X        | X                                                       |                            |
| SQUASH questionnaire (Physical activity undertaken)            |           | X        | X                                | X | X        | X         | X        | X                                                       |                            |
| Food diary (review diary)                                      |           | X        | X                                | X | X        | X         | X        | X                                                       |                            |
| TUG (Timed up and go test)                              |           | X        | X                                | X | X        | X         | X        | X                                                       |                            |
| Step count (review diary)                                      |           | X        | X                                | X | X        | X         | X        | X                                                       |                            |
| Acceptability of the study and proxy                           |           |          |                                  |   | X*       |           | X        | X                                                       |                            |
| SCLC treatment regimen and dose or interval adjustments        |           | X        | X                                | X | X        | X         | X        | X                                                       | X                          |
| Unplanned healthcare contacts (review diary)                   |           | X        | X                                | X | X        | X         | X        | X                                                       |                            |
| Response to cancer therapy for SCLC and adverse events         |           |          |                                  |   | X        |           | X        | X                                                       | X                          |
| Check compliance (review diary)                                |           |          | X                                | X | X        | X         | X        | X                                                       |                            |
| Dispense (D) new and/or return (R) unused medication for study |           | X
(D) |                                  |   | X
(R) | X
(D)  | X
(R) | X
(R)                                                |                            |

AKPS, Australia-modified Karnofsky Performance Status; BMI, Body Mass Index; ECG, Electrocardiogram; HbA1c, glycated haemoglobin, CPR, C-reactive protein; FAAct, Functional Assessment of Anorexia Cachexia Treatment; DEXA, dual x-ray absorptiometry; CT, computed tomography; FACIT-F, Functional Assessment of Chronic Illness Therapy-Fatigue; SQUASH, Short Questionnaire to Assess Health Enhancing Physical Activity; GIC, Global Impression of Change; CGI-S, Clinical Global Impression of Severity; CGI-I, Clinical Global Impression of Improvement; SCLC, small cell lung cancer. TUG – Timed Up and Go test.

a Occurs after the last dose of the study intervention (last day of data collection, or when treatment is ceased, if cessation prior to Week 12 or Week 24 occurs)

b First telephone follow-up visit will occur 7 days after the Week 12 or Week 24 (if did not elect to enter extension) visit or the early termination visit due to withdrawal if treatment was ceased early. Subsequent telephone follow-up visits will occur every 7 days thereafter for a period of 4 weeks. There will be 4 follow-up visits in total.

Informed consent will be obtained prior to any study-related screening procedures.

ICECAP-A will be administered after the EQ-5D-5L questionnaire

\*Only if people elect NOT to enter the extension.

^ All electronically stored data from chest CT scans whenever they are done clinically will be used for evaluation of change in muscle mass at the thoracic (T4) level.

**Table 6-2** Schedule of Study Assessments for caregivers (Screening to Week 12 and optional extension – Weeks 13-24)

| Assessment                         | Patient screening | Baseline       | Visit Day Treatment Period |   |                 | Extension |                |
|------------------------------------|-------------------|----------------|----------------------------|---|-----------------|-----------|----------------|
| Week                               |                   |                | 4                          | 8 | 12              | 18        | 24             |
| Visit                              | 1                 | 2              | 3                          | 4 | 5               | 6         | 7              |
| Informed consent       | X                 | X ^ |                            |   |                 |           |                |
| EQ-5D-5L - quality of life         |                   | X              |                            |   | X* § |           | X § |
| Carer Experience Scale (CES)       |                   | X              |                            |   | X* § |           | X § |
| Diary (daily records by caregiver) |                   | X              | X                          | X | X               | X         | X              |

Informed consent will be obtained prior to any study-related procedures.

^OR (if consent not obtained during visit 1)

\*Only if patient elect not to enter the extension.

§ Or withdrawal

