## 4.8 Cessation of study drug/intervention

Treatment may be ceased for one of the reasons listed below. A description of the reason behind ceasing the drug will be recorded in the medical record or clinical file as per the site's SOP.

- Reached primary endpoint (12/ 24 weeks).
- Participant request.
- Insertion of tube feeding or parenteral nutrition.

- Unacceptable side effects from study medications (defined by National Cancer Institute Common Criteria for Adverse Events; NCI-CTCAE version 5.0) of grade 3 not resolving with appropriate treatment or any grade 4 or 5 toxicities.
- An AE occurs that, in the opinion of the Investigator, makes it unsafe for the participant to continue in the study.
- Participants who in the opinion of the Investigator are not well enough to continue the study (specific reasons for cessation need to be documented in the data collection worksheet and electronic Case Report Form – eCRF).
- It is inappropriate to continue the study medicine for whatever reason.
- The participant or proxy withdraws their consent for continued administration of the study medication, with or without withdrawing consent from study and all protocol-specified assessments and follow-up procedures.
- The participant dies.
- The participant is lost to follow-ups.
- The Investigator, for any reason, terminates the entire study, or terminates the study for that participant; or the attending physician requests that the participant be withdrawn for any medical reason.
- The Sponsor or the Regulatory Authorities or the Ethics Committee(s), for any reason, terminates the entire study, or terminates the study for this trial site or participant.

If a participant prematurely discontinues treatment with anamorelin/placebo at any time prior to completing the 12-week visit, the Investigator must try his/her best to contact the person for scheduled visits. Every effort will be made to collect data from the protocol-specified assessments. Participants will be asked to continue to participate in the study and complete planned visits up to Week 12 even if they have permanently discontinued treatment with anamorelin/placebo (“retrieved dropout” approach). If participants discontinue study participation at any time, they will be asked if they can participate in one final clinical visit and whether they would participate in a follow-up telephone call seven days later.

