## 6.0 STUDY ASSESSMENTS

The study assessments are tabulated in Table 6-1. The study period will include 28 days after medication cessation (4 weekly follow-up period) or until death (whichever timeframe is shorter).

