## **8.10 End of treatment assessments**

Collection of end of treatment data will occur following the last dose of the study intervention (or when treatment is ceased, if earlier cessation occurs). During the visit, the study nurse will take the Week 12 measures and assessments as outlined in Table 6-1 of study measures and record the visit in the Data Collection Worksheet and eCRF. This visit will also be recorded within the participant clinical file, along with any instructions or changes regarding ongoing management.

If early cessation due to an AE, all associated documents will be completed (Serious Adverse Event (SAE) report, AE assessment score etc.).

An AE with a grade of 3 (that has not responded to symptomatic treatment instituted by the treating physician according to local protocols) or 4 will activate treatment cessation and an AE report will need to be completed and submitted. Please refer to Section 10 for further information about AE and SAE reports.

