### **8.12 Follow-up phase assessments**

All participants will be followed by their clinician for continuing care, irrespective of the point at which they exit the study. For all study participants, regardless of above choices, study outcomes and collection of data for economic evaluation will occur until the end of 12 weeks after randomisation, unless consent is withdrawn.

Participants will be followed up by telephone weekly irrespective of their place of care for 4 weeks or death or withdrawal of consent, whichever is the shorter period. The date of death will be collected from medical records even if this occurs after the 4-week follow-up. The contact data will be recorded in the follow-up Data Collection Worksheets and eCRF, and will provide data on compliance with cancer treatment, side effects and long term clinical and economic outcomes. The nurse will use the telephone number recorded in the discharge details and will clearly identify themselves. The nurse will ask for information as outlined in the data collection worksheets and will record this while talking with the participant. A medication list will be updated at each contact to record actual prescribed and taken medications since the preceding visit.

Date of death will be recorded for all participants collected from existing medical records.

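### The schedule ties the exit visit to stopping study drug, the retrieved-dropout rule keeps those participants on visits to Week 12, and nothing says which governs or how an early FAACT is used

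*Supplement*

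**What the plan says.** The current protocol (V1.6) gives two sets of instructions for a participant who stops study drug before Week 12.

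**Stopping drug treated as the trigger for exit**
- Table 6-1, footnote a, times the Exit/Early Termination visit after the last dose: "last day of data collection, or when treatment is ceased, if cessation prior to Week 12 or Week 24 occurs".
- Section 8.10 collects end-of-treatment data after the last dose, "or when treatment is ceased, if earlier cessation occurs", and adds that "the study nurse will take the Week 12 measures and assessments as outlined in Table 6-1".
- Table 6-1, footnote b, starts the weekly calls from the Week 12 or Week 24 visit, or from "the early termination visit due to withdrawal if treatment was ceased early". There are four calls, and the follow-up column has no FAACT entry.
- Section 6.0: "The study period will include 28 days after medication cessation (4 weekly follow-up period) or until death (whichever timeframe is shorter").

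**Stopping drug treated as compatible with staying in the study**
- Section 4.8, which names a retrieved-dropout approach, asks participants to "complete planned visits up to Week 12 even if they have permanently discontinued treatment".
- Section 3.4.3 encourages attendance at scheduled visits after drug is discontinued.
- Section 8.12: "study outcomes and collection of data for economic evaluation will occur until the end of 12 weeks after randomisation, unless consent is withdrawn".

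The first primary efficacy endpoint (section 5.1.3) is change in the 5-item anorexia domain of the FAACT from baseline to Week 12. Section 5.1.1 grades the proportion with complete primary endpoint data as green above 70%, orange from 60 to 70% and red below 60%. Section 10.3 rules out imputation. Section 10.1 says discontinued participants are not replaced.

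**The concern.** Section 8.9 sends the study nurse to Table 6-1 for what to do at each visit. A nurse working from that table and section 8.10 could in good faith carry out an exit visit when drug stops, make four weekly calls and close the participant. A nurse working from section 4.8 would keep the same participant on visits to Week 12. Identical participants would then yield different data depending on which section the site applied.

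Two harms are possible, and for any one participant they are alternatives:

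1. The cessation-day FAACT is not used as Week 12. The Week 12 value is then missing and completeness falls.
2. The cessation-day FAACT is used as Week 12. The participant then counts as complete, but the change score covers a shorter follow-up than everyone else's.

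Neither is likely to be random. The reasons for cessation in section 4.8 include unresolved or severe toxicity, tube feeding and being too unwell to continue, all plausibly related to appetite and possibly to arm.

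**Working it through.** **1. The plan's own figure.** Section 10.1 randomises 50 to have Week 12 data on 40. The implied loss is 1 − 40/50 = 20%, and 40/(1 − 0.20) = 50, so the figure reproduces. Expected completeness is 40/50 = 80%, green.

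**2. Side by side, for a participant who stops drug early and does not withdraw consent.**

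| Question | Footnotes a and b, 6.0, 8.10 | 3.4.3, 4.8, 8.12 |
|---|---|---|
| Is there an exit visit at cessation? | Yes (footnote a, 8.10) | Final visit is for those who leave the study |
| Do planned visits continue to Week 12? | Not stated | Yes |
| When do the four weekly calls start? | Can be read as from cessation | Not tied to cessation of drug |
| Is an early FAACT the Week 12 value? | Not stated | Not stated |

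No passage ranks the two columns or says whether such a participant has both an exit visit and Visit 5.

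**3. Reach of the 28-day reading.** If the study period closed 28 days after cessation, closing week = stopping week + 4.

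| Stop at week | Closes at week | Reaches Week 12? |
|---|---|---|
| 2 | 6 | No |
| 4 | 8 | No |
| 6 | 10 | No |
| 8 | 12 | Yes |
| 10 | 14 | Yes |

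Even on this reading, Week 12 is cut off only for stops before about Week 8. For later stops the remaining risk is a mistimed FAACT.

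**4. Margin in the completeness criterion.** I take all 50 randomised as the denominator, which is an assumption because section 5.1.1 does not specify one. Starting from 40/50:
- four more lost: 36/50 = 72%, green;
- five more lost: 35/50 = 70%, orange;
- ten more lost: 30/50 = 60%, still orange;
- eleven more lost: 29/50 = 58%, red.

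**5. Range over assumed early-stopping rates.** The documents give no rate, so these are illustrations only. Suppose a fraction s stop early, none of them has a Week 12 FAACT, and other loss is 20% among the rest. Completeness is then (1 − s) × 0.80:
- s = 10%: 0.90 × 0.80 = 72% (36/50), green;
- s = 20%: 0.80 × 0.80 = 64% (32/50), orange;
- s = 30%: 0.70 × 0.80 = 56% (28/50), red.

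With no other loss, the same rates give 90%, 80% and 70%. If section 4.8 is followed, stopping drug does not by itself lower completeness. These figures assume that every site applies the table over section 4.8, so they are an upper bound on the effect at each rate.

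**The case against.** The best defence is that the intention is plain. Three sections keep early stoppers in the study, and 8.12 does so for all participants unless consent is withdrawn. The passages on the other side are softer than a quick reading suggests:

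- Footnote b refers to an early termination visit due to withdrawal. The column heading and section 8.11 also attach those assessments to withdrawal, so the call schedule need not start for someone who only stops drug.
- Section 6.0 says the study period will include the 28 days, which can mean a minimum safety window and not an end point.
- Footnote a offers alternatives. It does not cancel Visits 3 to 5.
- The Week 12 measures in 8.10 may simply name a list of assessments. Section 9.4.2 lists separate Treatment Cessation and Withdrawal worksheets, and section 9.4.3 describes validation rules on expected visit dates.
- The traffic lights are indicative, the between-arm analysis is exploratory, and on-time, on-dose completion is less exposed because cancer-treatment adjustments are also recorded at follow-up.

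Much of this stands. A reader might infer that the plan closes every early stopper 28 days after the last dose and so removes Week 12 for all of them. The documents do not support that: loss or mistiming occurs only where a site applies footnote a and 8.10 over 4.8.

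The defence does not resolve footnote a and 8.10 themselves. Both are triggered by ceasing treatment, not by withdrawal, and so blur the distinction that 3.4.3 and 4.8 draw. Nor does it supply a rule for using a FAACT taken at early cessation.

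**Conclusion.** The inconsistency is real and sits in the current text. It can cost or mistime the Week 12 FAACT for participants who stop drug early; it does not do so by prescription. The sample size is not wrong on this point.

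The size depends on how many people stop early and how many sites follow the schedule over section 4.8, and the documents give neither. What can be said without an assumed stopping rate is that the planned 80% completeness has little slack. With all 50 as denominator, five further lost values move the criterion to orange and eleven to red. If early scores are instead accepted as Week 12 values, completeness is preserved on paper while the endpoint mixes follow-up times. With no imputation, a value not collected at Week 12 cannot be recovered, so the passages should be reconciled promptly.

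**What to change.** Reconcile the passages so that the retrieved-dropout rule governs data collection:

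1. **Table 6-1, footnotes a and b.** State that stopping drug alone is not study exit, and that Visits 3 to 5, including FAACT, continue at their original dates to Week 12.
2. **Section 6.0.** State that the study period does not end before the Week 12 visit unless the participant dies or withdraws consent for assessments. The 28 days after last dose remain included.
3. **Section 8.10.** State that any FAACT taken at early cessation is recorded under its actual date and is not used as the Week 12 value.
4. **Section 5.1.1 or 10.3.** Repeat that rule where completeness and the primary endpoint are defined, so that both count only a FAACT from the Week 12 visit.

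The clinical content of the cessation visit is for the sponsor to decide. The cost is a wording amendment, a visit label in the eCRF and a note to sites. No visit is added beyond those that section 4.8 already asks for.
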